**Fig. 1 Fig1:**
[figure not shown]
Flow of patients through the KEATING trial

### Dietary intervention

The dietary intervention will commence following surgery and prior to starting chemoradiotherapy. Oncology treatment will continue in line with the standard of care.

Both MKD and MCT KD are high in fat and low in carbohydrate. However, they contain different amounts and types of fat. The MKD provides fat to 80% of total energy requirements (predominately long-chain fatty acids) and 5% carbohydrate. Whilst the MCT KD provides fat to 75% of total energy requirements (30% of which is medium chain fatty acids, consumed via a nutritional supplement), and 10% carbohydrate. Protein is allowed freely in both diets.

Patients (and relatives when appropriate) will receive dietetic counselling and be provided with dietary literature to calculate intakes of these food groups. All patients will commence the diet at home, without a fasting start.

Energy requirements will be appropriate for patient’s age, weight, activity and metabolic stress, monitored through weight checks. To estimate energy requirements a 3-day weighed food diary will be analysed using DietPlan 7© (Forestfield Software LTD, Horsham, UK) and compared to the Parenteral and Enteral Nutrition Group (PENG) energy requirements [23–29], from which a mean energy requirement will be estimated. The requirements can be tailored for weight loss, gain or maintenance dependent upon the patient’s needs and wishes. Dietary requirements will be recalculated each time a new weight is obtained.

Seven-day diet plans will be calculated by the dietitian based upon total energy requirements. Nutritional content will be analysed using DietPlan 7© (Forestfield Software LTD, Horsham, UK) to ensure appropriate proportions of carbohydrate, fat and protein.

### Associated medications and treatments

Medications permitted: all medications with the exception of those specified below.

Medications not permitted: weight loss medications (including Orlistat, Belviq, Contrave, Saxenda, Phentermine and Qsymia) and any agents used in diabetic therapy (including biguanides, sulfonylureas, meglitinide derivatives, alpha-glucosidase inhibitors, thiazolidinediones (TZDs), glucagon-like peptide–1 (GLP-1) agonists, dipeptidyl peptidase IV (DPP-4) inhibitors, selective sodium-glucose transporter-2 (SGLT-2) inhibitors, insulins, amylinomimetics, bile acid sequestrants and dopamine agonists).

Data will be collected on use of corticosteroids, antiemetics, laxatives and antiepileptic drugs. Data will also be collected for nutritional supplements consumed by the patient.

### Baseline data collection

Baseline data will be collected at the initial consultation once eligibility is confirmed and written consent obtained by the investigator. Baseline data will include past medical history, symptoms at presentation, tumour location, surgical procedure, histopathology and molecular pathology subtypes for glioblastoma (MGMT, IDH-1, ATRX, 1p/19q status), current medication (prescribed and purchased), current nutritional supplementation (vitamins, minerals, herbal and nutritional products), food allergies or intolerances, level of physical activity (as defined by DH [25]), food or fluid texture modification, use of enteral feeding tube, anthropometry (height, weight, BMI, mid-arm muscle circumference, triceps skinfold, mid-arm muscle circumference, hand grip strength, waist circumference and fat mass), biochemistry (fasting lipid, fasting glucose, liver, renal and bone profiles), habitual 3 day weighed food diary, habitual gastrointestinal complaints, quality of life measures (EORTC QLQ C30 and QLQ BN 20 questionnaires) and habitual food acceptability (Food Acceptability Questionnaire, [30]).

Histopathology and molecular pathology subtypes for glioblastoma (MGMT, IDH-1, ATRX, 1p/19q status) classification will be conducted as per the current standard of care.

MRI will be conducted as per the current standard of care for patients with GB [31], resulting in scans at the following intervals:Pre-surgeryPost-surgery (within 72 h)Pre-radiotherapy1 month post-radiotherapyMid chemotherapy (after 3 cycles)Post-chemotherapy (after 6 cycles)Every 6 months from 12 to 24 months

MRI scans will include T1 ± gadolinium, T2 and fluid-attenuated inversion recovery (FLAIR) sequences. Extent of resection on post-operative MRI will be determined, and recurrence will be measured according to the Response Assessment in Neuro-Oncology (RANO) criteria [32].

Changes to medications and treatment will be recorded; these are permitted to be altered in-line with the treating oncologist/neurosurgeons recommendations. Details of concomitant radiotherapy and chemotherapy and adjuvant chemotherapy will be noted in the CRF.

### Primary outcome measures

Assess retention and drop-out rates defined as:The number of patients who start randomised treatment as a proportion of the number randomised, with reasons for non-compliance.The number of patients who complete 12 weeks of diet as a proportion of the number randomised, with reasons for non-compliance.The time to dietary discontinuation (week 12 or duration to discontinuation if prior to this).A description of barriers and facilitators to data collection and participant retention will also be included.

### Secondary outcome measures

Estimation of recruitment ratesActual recruitment rates will be compared to the proposed recruitment figures (12 patients over 12 months) with purpose of demonstrating trial feasibility for future, potential phase III clinical trials.
Enrolment of patientsAbility to comply with protocol enrolment timelines will be assessed by the number of patients initiated on diet prior to starting chemoradiation treatment. This will inform the feasible timelines in future clinical trials.
Long term retentionThe time to dietary discontinuation after week 12.
Dietary adjustments required to achieve ketosisDietary adjustments advised by the dietitian will be recorded in the case report form (CRF) to inform the macronutrient composition of MKD and MCT KD required to achieve ketosis in this population to inform future protocols.
Dietary complianceDietary compliance will be self-reported by the patient at clinic appointments. The dietitian will also analyse self-reported 3-day weighed food diaries (completed at weeks 6, 12 and every 3 months thereafter) using DietPlan 7© (nutritional analysis computer programme). The results will be compared to dietary fat and carbohydrate requirements (calculated at previous clinic appointment) and percentage compliance rates will be calculated.
MCT complianceMCT supplement compliance will be self-reported through 3-day weighed food diaries collected at week 6, week 12 and every 3 months thereafter. The results will be compared to the MCT dose advised (at previous clinic appointment) and a percentage compliance rate will be calculated.
Ketone and glucose levelsKetosis will be monitored by patients self-reporting urinary ketone levels twice per day for the first 6 weeks then then once per week thereafter. Adequate urinary ketosis is defined as ≥ 4 mmol/L.Blood ketones and blood glucose levels will be monitored weekly. Adequate blood glucose levels are defined as 3–5 mmol/L.There are no robust guidelines for adequate levels of blood ketosis in adults with GB, however, from preliminary work by Meidenbauer et al. [33], levels of 2–4 mmol/L to be beneficial, therefore patients will be asked to record levels to aid future research.All figures will be recorded in the ketone/glucose diary provided. The dietitian will assess these at each point of contact.
Dietetic time required for the interventionsDietetic time spent on both clinical and non-clinical activities related to the trial will be recorded to aid future protocol design.
Protocol refinements requiredDeviations from the protocol will be documented on the deviation log. This will be used to refine future protocols and inform future clinical trials.
 Sample size estimates for future trialsData synthesised from this pilot will inform sample size calculations for future phase III clinical trials based on the primary outcome measure of retention.
 Completeness of data for all trial outcomesCompleteness of documented data will be assessed to inform feasibility of future clinical trials.
 Quality of lifeQuality of life will be evaluated though the generic EORTC QLQ C30 and brain cancer-specific QLQ BN 20 validated questionnaires prior to commencing the diet, at week 6, week 12 and every 3 months thereafter or at point of dietary discontinuation if prior to this.
 Food acceptabilityFood acceptability will be assessed through the non-validated Food Acceptability Questionnaire [30] completed prior to commencing the diet, at week 6, week 12 and every 3 months thereafter or at point of dietary discontinuation if prior to this.
 Gastrointestinal side effectsGastrointestinal side effects will be quantified from the EORCT QLQ C30 questionnaire and through informal clinic assessments. The Common Terminology Criteria for Adverse Events ([CTCAE], version 4.0) will be used to grade gastrointestinal side effects.
 Changes to biochemical markersBiochemical markers (fasting lipid, fasting glucose, liver, renal and bone profiles) will be undertaken at baseline and repeated every 3 months until discontinuation of diet.
 Anthropometric changesAnthropometry (height, weight, body mass index (BMI), waist circumference, mid-upper arm circumference (MUAC), mid-arm muscle circumference (MAMC), tricep skinfold (TSF), hand grip strength (HGS) and fat mass) will be measured at baseline, week 6, week 12 and every 3 months thereafter. All measurements will be undertaken as per measurement methodology cited in Parenteral and Enteral Nutrition Group (PENG), pocket guide to clinical nutrition [29].

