### Intervention design

All participants will be invited to attend clinical consultations pre-diet, on initiating diet, 6 weeks from initiation, 12 weeks from initiation (primary completion) and every 3 months for a total of 12 months (secondary completion) or until dietary discontinuation if prior to this. Telephone consultations will take place post initiation at weeks 1, 3 and 9 to enable dietary ‘fine tuning’ (Table 1 and Fig. 1). All consultations will be undertaken with the same research dietitian. It is not possible to blind the participants or the investigators due to differences between the diets and dietary education required.

**Table 1 Tab1:** Study schedule

	Study period										
		Enrolment/diet allocation	Post allocation (on diet)								Close out
Timeline		1 week post-histology	1 week after clinic 1	1 weeks after clinic 2	3 weeks after clinic 2	6 weeks after clinic 2	9 weeks after clinic 2	12 weeks after clinic 2	6 months after clinic 2	9 months after clinic 2	12 months after clinic 2
Visit window	Post-histology	± 5 days	± 5 days before radiotherapy	± 3 days	± 3 days	± 5 days	± 3 days	± 5 days	± 10 days	± 10 days	± 10 days
Clinic visit	Telephone discussion	Clinic appointment 1 Consent, register, baseline assessment, randomisation	Clinic appointment 2 Commence diet	Telephone review 1	Telephone review 2	Clinic appointment 3 Diet review	Telephone review 3	Clinic appointment 4 Diet review	Clinic appointment 5 Diet review	Clinic appointment 6 Diet review	Clinic appointment 7 Diet review End of trial
Information sheet	X										
Informed consent		X									
Eligibility screen		X									
Randomisation		X									
Medical history review		X									
Medications review		X									
Anthropometry		X				X		X	X	X	X
Biochemistry		X						X	X	X	X
Food diary		X				X		X	X	X	X
Ketone diary						X		X	X	X	X
Quality of life (QoL) questionnaire EORCT QLQ C30		X				X		X	X	X	X
QoL questionnaire QLQ BN20		X				X		X	X	X	X
Food Acceptability Questionnaire		X				X		X	X	X	X
Dietary review		X	X	X	X	X	X	X	X	X	X
Ketone review				X	X	X	X	X	X	X	X

X = procedure carried out

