### Adverse events

The main health risks associated with the diet include gastrointestinal intolerance (such as diarrhoea, constipation, nausea, reflux, abdominal discomfort), altered or raised cholesterol, kidney stones and decreased bone density [44].

To monitor these health risks biochemistry will be monitored every 3 months (renal, bone, LFT, fasting cholesterol and glucose). Gastrointestinal side effects will be assessed using the Common Terminology Criteria for Adverse Events (CTCAE, version 4, [45]), and dietary adjustments will be made to aid symptom relief when possible.

All adverse events (AE) will be reported. The National Institute of Health Research (NIHR) ‘decision tree for adverse event reporting’ [46] will be used to grade AE and serious adverse events (SAE) severity.

An AE or SAE will be reported by the investigator; however the chief investigator will be responsible for determining causality. The trial would close early should SAEs occur as a direct result of the trial intervention.

Trigger monitoring will be adopted which will be managed by the University of Liverpool (the Sponsor).

All SAE will be reported to the Trial Steering Committee within 1 week of the event.

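### Compliance at weeks 6 and 12 is scored against the target from the previous clinic appointment, although telephone reviews may have changed the advice since then

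*Protocol article*

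**What the plan says.** The Secondary outcome measures section defines two compliance percentages, both from 3-day weighed food diaries at week 6, week 12 and every three months after that.

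- MCT supplement: "The results will be compared to the MCT dose advised (at previous clinic appointment) and a percentage compliance rate will be calculated".
- Fat and carbohydrate: "The results will be compared to dietary fat and carbohydrate requirements (calculated at previous clinic appointment) and percentage compliance rates will be calculated".

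The Intervention design section puts on-diet clinic visits at these times: "on initiating diet, 6 weeks from initiation, 12 weeks from initiation (primary completion) and every 3 months for a total of 12 months". It adds calls between them: "Telephone consultations will take place post initiation at weeks 1, 3 and 9 to enable dietary" fine tuning. Table 1 names these contacts telephone reviews, apart from the numbered clinic appointments, and marks a dietary review and a ketone review at each.

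Other passages show that advice may change between clinic visits. On the ketone and glucose diary: "The dietitian will assess these at each point of contact". Under Adverse events, for gastrointestinal symptoms: "dietary adjustments will be made to aid symptom relief when possible". Changes made to reach ketosis are a secondary outcome in their own right, and the "adjustments advised by the dietitian will be recorded in the case report form (CRF").

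**The concern.** The denominator of a compliance percentage should be the target the patient was asked to meet on the days the diary was kept. Here it is the target from the last clinic visit, and a call intended for adjusting the diet can come in between. Whenever such a call changes the target, intake under the new advice is divided by the old one.

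The measure can then put patients in the wrong order: one who does what the dietitian last said moves away from 100%, while one who disregards it stays at 100%. The Rationale and the Conclusion both present the trial as the means of learning which of the two diets patients keep to better. Weeks 6 and 12 are the only on-diet diaries up to primary completion, and both have a call before them.

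**Working it through.** The article states no figure for compliance or for the size of adjustments, so there is none to reproduce. The check has three parts.

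**1. Which target applies to which diary** (visit times from Intervention design and Table 1)

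| Diary | Previous clinic appointment | Telephone reviews in between |
|---|---|---|
| Week 6 | Clinic 2 (week 0) | Weeks 1 and 3 |
| Week 12 | Clinic 3 (week 6) | Week 9 |
| Month 6 | Clinic 4 (week 12) | None scheduled |
| Month 9 | Clinic 5 (month 6) | None scheduled |
| Month 12 | Clinic 6 (month 9) | None scheduled |

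Two of the five on-diet diaries are exposed. The visit windows do not alter the order. The latest week-3 call is day 21 + 3 = 24 and the earliest week-6 visit is day 42 − 5 = 37. The latest week-9 call is day 63 + 3 = 66 and the earliest week-12 visit is day 84 − 5 = 79. If the diary covers the three days before the visit (assumed), it starts no earlier than day 34 or day 76, ten days after the call in each case.

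**2. Effect on one patient's score**

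Let T be the target at the previous clinic appointment and fT the target after the call or calls.

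- Follows the new advice exactly: intake fT, score = 100 × fT / T = 100f%. True compliance is 100%.
- Keeps to the old target: intake T, score = 100%. True compliance with the current advice is 100 × T / fT = 100/f%.

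| f (assumed) | Score, follows new advice | Score, keeps old target | True compliance of the latter |
|---|---|---|---|
| 0.7 | 70% | 100% | 142.9% |
| 0.8 | 80% | 100% | 125.0% |
| 0.9 | 90% | 100% | 111.1% |
| 1.0 | 100% | 100% | 100% |
| 1.1 | 110% | 100% | 90.9% |
| 1.2 | 120% | 100% | 83.3% |
| 1.3 | 130% | 100% | 76.9% |

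The upper end does not fit every component. At constant energy, f = 1.3 for fat would mean 80% × 1.3 = 104% of energy in the modified diet. In the MCT diet it would mean 75% × 1.3 = 97.5%, which exceeds 100% once the 10% carbohydrate is added. Large upward factors are therefore arithmetically possible only for carbohydrate or the MCT dose.

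**3. Effect on an arm mean**

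Twelve patients allocated 1:1 give about six per arm. If one fully adherent patient has f = 0.75 (assumed), the arm mean falls by (100 − 75) / 6 = 4.2 points. Two such patients lower it by 8.3 points. Upward changes move it the other way.

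**The case against.** Several counter-arguments narrow the point.

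- **A call need not change a target.** Fine tuning may mean food choices within unchanged targets. This stands: the diaries can be affected, but the article does not say that they will be.
- **Fat and carbohydrate are the weaker case.** Their comparator is a calculated requirement, and under Dietary intervention "Dietary requirements will be recalculated each time a new weight is obtained". Table 1 schedules anthropometry only at clinic appointments, so on this reading a call leaves the requirement as it was. This stands in part. The article also expects macronutrient composition to be altered to reach ketosis, and ketones are reviewed at every contact, so a change by telephone is possible. For the MCT dose the comparator is the advised dose itself, and the conflict is direct.
- **The term clinic appointment might be shorthand for any contact.** The Table 1 row headed as clinic visits does include the telephone reviews. But its entries are labelled separately, and the plain reading excludes the calls.
- **The consequence is limited.** Compliance is one of many secondary outcomes and is summarised descriptively. Self-reported compliance at clinic does not depend on this denominator. The promised detailed analysis plan could still correct the rule. All of this stands and bears on weight; the rule as printed remains wrong.

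Two stronger readings are tempting. A reader might infer that patients who follow the latest advice will be classed as non-compliant. The article sets no cut-off, and a followed increase scores above 100%. A reader might also infer that the comparison of diets is biased. The article gives no frequency or direction of adjustment by arm, raised and lowered targets shift scores in opposite directions, and MCT compliance has no counterpart in the other arm. Bias is possible but not shown.

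**Conclusion.** The point holds in limited form. As written, the rule scores the week-6 and week-12 diaries against superseded advice whenever a telephone review has changed the target. A patient who follows a change by factor f exactly then scores 100f%, which is 70% to 130% for assumed f of 0.7 to 1.3, and a patient who ignores the change scores 100%. These sizes are illustrative, because the article reports neither how often nor by how much targets change.

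The conclusion rests on reading clinic appointment as Table 1 labels it and on at least some calls changing a target. It is firm for the advised MCT dose and conditional for fat and carbohydrate. The diaries at months 6, 9 and 12 have no scheduled call before them. The descriptive comparison of adherence could be distorted if one diet is adjusted more often. The primary outcome (retention) and the traffic-light criteria do not use these percentages. It is worth correcting because the rule is explicit and adherence is part of the trial's stated purpose.

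**What to change.** For MCT dose, fat and carbohydrate, replace the reference to the previous clinic appointment with: *most recently advised at any contact, clinic or telephone, before the first diary day*. Take that target from the adjustments recorded in the CRF. The article says this for changes made to reach ketosis, so state that changes made for symptom relief are recorded there too, with the date and the new target. State how scores above 100% are summarised, for example whether they are left as they are, capped, or reported as absolute deviation from target.

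The cost is a wording change, which the analysis plan still to be written can carry, and slightly more data handling to match each diary to the target in force. No visit, procedure or dietary rule changes.

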## Rationale

The effect of lifestyle factors (including diet) on tumours is one of the top 10 priority areas for research identified by the James Lind Priority Setting Partnership in the Neuro-Oncology community [20]. To enable an adequately powered randomised controlled trial to be undertaken, investigating the efficacy of the ketogenic diet in the therapeutic management of glioblastoma, this preliminary study is important to test protocol methodology and to explore potential impact on patient quality of life and health. At present, it is not known which KD, if any, holds promise for further investigation of effectiveness. Therefore, this study will directly compare two KD (MKD and MCT KD) to determine which diet is most deliverable and best adhered to by patients in order to test clinical effectiveness, as a primary outcome (overall survival) in a future definitive trial, within an NHS glioblastoma population. In a trial of effectiveness, a control group would be required (such as ‘healthy eating’) and directly compared to the ‘successful’ dietary arm from this pilot.

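### From week 12 onward, diet and MCT compliance are scored against a target that may already have been reduced, so 100% can be recorded when the diet as defined was not delivered

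*Protocol article*

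**What the plan says.** Under Secondary outcome measures, two percentage compliance rates are defined from 3-day weighed food diaries completed at weeks 6 and 12 and every 3 months thereafter.

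- Diet, both arms: "The results will be compared to dietary fat and carbohydrate requirements (calculated at previous clinic appointment) and percentage compliance rates will be calculated".
- MCT supplement, MCT KD arm only: "The results will be compared to the MCT dose advised (at previous clinic appointment) and a percentage compliance rate will be calculated".

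The target can change for several reasons. For gastrointestinal side effects, the Adverse events section says that "dietary adjustments will be made to aid symptom relief when possible". The Dietary intervention section says: "Dietary requirements will be recalculated each time a new weight is obtained". Intervention design provides telephone fine tuning at weeks 1, 3 and 9. Secondary outcome measures also lists adjustments made to reach ketosis, which are recorded in the CRF and used to describe the composition each diet needs.

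A fixed reference exists. The Dietary intervention section defines the MKD as 80% fat and 5% carbohydrate, and states for the other arm: "MCT KD provides fat to 75% of total energy requirements (30% of which is medium chain fatty acids, consumed via a nutritional supplement), and 10%" (the last figure is the carbohydrate share). Neither compliance rate is stated against that composition or against the starting prescription.

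The Rationale gives the purpose of comparing the diets: "to determine which diet is most deliverable and best adhered to by patients". The Conclusion repeats it.

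**The concern.** A rate whose denominator is the latest clinic target measures whether the patient followed the advice. It does not measure whether the diet under test was delivered. When the target has been lowered because the diet was not tolerated, the two separate: intolerance lowers the denominator, and the rate stays at or returns to 100%. The pilot is meant to say which diet is more deliverable as well as better followed, and this percentage cannot answer the first part from week 12 onward.

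A related problem affects the adjustments outcome. It is framed around reaching ketosis, and the article does not separate those changes from cuts made for symptoms. If they are summarised together, reductions made for intolerance would feed into the composition reported as needed for ketosis.

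**Working it through.** The plan gives no figure for compliance. Its one statistical figure, ± 25.93% for 70% retention with n = 12, reproduces (1.96 × √(0.7 × 0.3 / 12) = 25.93 points), but this point does not depend on it.

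**Which clinic supplies the denominator** (Table 1)

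| Diary | Previous clinic | Telephone reviews in between |
|---|---|---|
| Week 6 | Clinic 2, diet start | Weeks 1 and 3 |
| Week 12 | Clinic 3, week 6 | Week 9 |
| 6 months | Clinic 4, week 12 | None |

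The week 6 score therefore uses the starting prescription. A telephone cut at week 1 or 3 lowers that score. From week 12, the denominator can be a target already reduced at a clinic.

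**One patient.** Rate as written = intake / target set at the previous clinic. Assume that a fraction c is cut from the advised MCT, that the lower target is set at the week 6 clinic, and that everything advised is taken. With starting dose D:

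- Week 12 as written: D(1 − c) / D(1 − c) = 100% for any c.
- Week 12 against the starting dose: D(1 − c) / D = 75%, 50% or 25% for c = 25%, 50% or 75%.

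**Apparent improvement.** Assume the dose is halved by telephone at week 1 or 3, followed fully, and confirmed at the week 6 clinic. Week 6 is 0.5D / D = 50%. Week 12 is 0.5D / 0.5D = 100%. Intake has not changed.

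**Measure common to both diets.** The MCT rate exists in one arm, so a comparison between diets must use the fat and carbohydrate rates. Assume MCT is halved in 3 of 6 MCT KD patients, no other fat replaces it, the fat target is lowered to match, all advice is followed, and the energy requirement is unchanged. The stated 30% MCT share can be read in two ways.

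- MCT as 30% of energy: fat falls from 75% to 75 − 15 = 60% of energy. 60 / 75 = 80% in cut patients. Mean (3 × 100 + 3 × 80) / 6 = 90%.
- MCT as 30% of the fat: MCT is 0.30 × 75 = 22.5% of energy. Fat falls to 75 − 11.25 = 63.75%. 63.75 / 75 = 85% in cut patients. Mean (3 × 100 + 3 × 85) / 6 = 92.5%.

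The written fat rate is 100% under both readings. If other fat does replace the MCT, fat delivery is 100% on either reference and the written MCT rate is also 100%. Mean MCT delivery is (3 × 100 + 3 × 50) / 6 = 75% of the starting dose, and neither written rate shows it.

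**The case against.** The strongest reply is that scoring intake against the individual prescription is a coherent definition of compliance, and that the reference is the previous clinic, not whatever was last advised. Both points are right. At week 6 the score is close to what a fixed reference would give, and an early or week 9 telephone cut pushes the next score down, not up. A reader might infer that every compliance figure is inflated. The schedule does not support that.

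The article also does not say in terms that the fat target or MCT dose is lowered for symptoms. It speaks only of dietary adjustments, and its explicit recalculation rule is by weight. The link is an inference, though a reasonable one: the MCT definition ties the dose to a particular clinic, which implies that it can change.

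A reader might also infer that the less tolerable diet would be ranked first and carried into phase III. The documents do not support that either. Setting the MCT supplement rate beside an MKD intake rate compares different measures. On fat, in the example above, the ranking would change only if the MKD rate lay between 90% (or 92.5%) and 100%. The traffic-light criteria under Defining success use retention, acceptability, data completeness, recruitment and commencement, not compliance. Gastrointestinal effects, food acceptability, ketone levels and adjustments are collected as well, and the analysis is descriptive.

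Finally, the CRF and the detailed analysis plan are not shown, and the CRF may already hold a reason for each adjustment. Its absence from the article is not a fault.

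The denominator itself remains. It is a stated outcome definition, not detail left for later. The progression criteria grade each diet separately and give no rule for choosing between two diets that both pass, so descriptive adherence may well bear on the choice.

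**Conclusion.** The point holds for week 12 and later. A reduction set at a clinic and then followed scores 100%, whatever its size. A telephone cut later confirmed at clinic makes compliance appear to rise (50% to 100% for a halved dose) with unchanged intake. On the measure shared by both diets the gap is more modest: 90% to 92.5% delivered against 100% as written, under the stated assumptions about how many patients are cut, by how much, with full uptake, a matching lower fat target and no replacement fat. The true size depends on how often targets are reduced, which the article cannot say.

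The consequence is limited to the descriptive judgement of which diet is better followed and more deliverable. The week 6 score, the retention outcome and the go/review/stop grading are unaffected. The change is worth making because it is cheap and bears on a stated purpose of the pilot.

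**What to change.** - Keep both rates as compliance with advice.
- From the same diaries, also report by diet at week 12 and later the intake of fat, carbohydrate and, for MCT KD, MCT as a percentage of the starting prescription or of the composition in the Dietary intervention section at the patient's current energy requirement. The second choice keeps weight-driven recalculation from being read as under-delivery. If it is used, state which reading of the 30% MCT share applies.
- Summarise symptom-driven changes separately from ketosis-driven ones, and let only the latter inform the composition reported as needed for ketosis. If the CRF does not already record the reason for each change, this needs one field, completed when the change is made.
- Judge adherence on both percentages: the first shows whether advice was followed, the second whether the diet was delivered as defined.

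The cost is one more descriptive column from data already analysed, and adherence figures that may look less favourable. No visit, dose or clinical rule changes.
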